## Abstract

**Background:**

The estimated 300,000 adults in Australia with severe mental illness (SMI) have markedly reduced life expectancy compared to the general population, mainly due to physical health comorbidities. Cardiovascular disease (CVD) is the commonest cause of early death and people with SMI have high rates of most modifiable risk factors, with associated quality of life (QoL) reduction. High blood pressure, smoking, dyslipidaemia, diabetes and obesity are major modifiable CVD risk factors. Poor delivery of recommended monitoring and risk reduction is a national and international problem. Therefore, effective preventive interventions to safeguard and support physical health are urgently needed in this population.

**Methods:**

This trial used a rigorous process, including extensive piloting, to develop an intervention that delivers recommended physical health care to reduce CVD risk and improve QoL for people with SMI. Components of this intervention are integrated using the Flinders Program of chronic condition management (CCM) which is a comprehensive psychosocial care planning approach that places the patient at the centre of their care, and focuses on building their self-management capacity within a collaborative approach, therefore providing a recovery-oriented framework. The primary project aim is to evaluate the effectiveness and health economics of the CCM intervention. The main outcome measures examine CVD risk and quality of life. The second aim is to identify essential components, enablers and barriers at patient, clinical and organisational levels for national, sustained implementation of recommended physical health care delivery to people with SMI. Participants will be recruited from a community-based public psychiatric service.

**Discussion:**

This study constitutes the first large-scale trial, worldwide, using the Flinders Program with this population. By combining a standardised yet flexible motivational process with a targeted set of evidence-based interventions, the chief aim is to reduce CVD risk by 20%. If achieved, this will be a ground-breaking outcome, and the program will be subsequently translated nationwide and abroad. The trial will be of great interest to people with mental illness, family carers, mental health services, governments and primary care providers because the Flinders Program can be delivered in diverse settings by any clinical discipline and supervised peers.

**Trial registration:**

Australian and New Zealand Clinical Trials Registry, ACTRN12617000474358. Registered on 31 March 2017.

**Electronic supplementary material:**

The online version of this article (10.1186/s13063-018-2748-7) contains supplementary material, which is available to authorized users.

## Background

The estimated 300,000 adults in Australia with a severe mental illness (SMI) such as schizophrenia, schizoaffective disorder, bipolar disorder, and depressive psychosis have markedly reduced life expectancy compared to the general population. Importantly, the impact on life expectancy primarily occurs because of physical health comorbidities, where international and local studies show life expectancy is curtailed by 13 to 30 years [1]. Cardiovascular disease (CVD) is common among people with SMI, and is the cause of many early deaths and reduced quality of life [1]. However, a high proportion of this population have readily modifiable CVD risk factors, such as high blood pressure (BP), smoking, dyslipidaemia, diabetes and obesity, where smoking is a key target [2]. A recent survey of Australians (M_age_ = 38 years) with psychotic disorders confirmed their high CVD risk status continues as 76% of those sampled were overweight/obese, had very low physical activity levels, 67% were current smokers, and 47% hypertensive. Analysis of fasting bloods identified that almost 50% had abnormal high density lipoprotein cholesterol and triglyceride levels, and almost 33% had raised glucose [3]. Poor delivery of recommended monitoring and risk reduction is a global problem, again highlighted by a more recent audit [4]. Therefore, effective preventive interventions is urgently needed for people with SMI to support their physical health [5].

However, improving physical health in people with SMI is complicated [6]. Acknowledging this, we adopted the UK Medical Research Council (UK MRC) to help structure the multistep, iterative development and evaluation of our complex intervention [6]. Below, we describe (A) identifying the evidence base, (B) identifying/developing theory, and (C) feasibility stage piloting. Assessment of the intervention using a randomised control trial, rigorous process evaluation, economic evaluation, and contextualising information will underpin the translation of the program into practice.

### Identifying the evidence base

Strategies to improve preventive and physical health management services have focused on either mental and physical health service integration or changing the health behaviours of patients with SMI. Overall, there has been a wide variety of intervention targets and methods, but few studies measure outcomes directly related to CVD risk, and there is little economic evidence of intervention cost effectiveness [5]. Systematic reviews of service integration [7] and cardio-metabolic risk interventions in SMI [8–12], Australian risk reduction guidelines from the National Vascular Disease Prevention Alliance, and reviews of newer technology-based interventions in SMI [13] and mixed populations [14–16], show a need for trials of well-founded clinical systems combined with behaviour change interventions with follow up beyond 12 months [10]. Trials must specifically measure CVD risk among those with SMI and include tailored evidence-supported intervention elements as follows:Health system improvements [7, 10];Tailored interventions for CVD risk-related behaviours [8, 10–12, 17];2.1.Tobacco quitting programs with pharmaceutical and structured behavioural support;2.2.One-on-one behavioural support for triglyceride reduction and diabetes control;2.3.One-on-one behavioural support and group interventions for weight reduction;2.4.BP-lowering and lipid-lowering pharmacotherapy according to Australian guidelines;Evidence-informed web-based and mobile technology support options (such as motivational text message prompts) for behaviour change [13–16].

In Australia, Baker et al. [18] recently trialled an intervention comprising nicotine replacement therapy (NRT), information provision, and an intensive programmed group intervention addressing multiple smoking risk-factors. Among smokers with SMI the intervention was no more effective than the control condition comprising NRT, information provision and telephone-delivered attention [18]. Other multiple risk-factor approaches now need to be tested in Australia; approaches which provide a sound clinical system *and* are fully consistent with the above intervention elements.

### Identifying/developing theory

Recovery-based mental health care is a broad approach oriented towards offering patients connectedness, hope and optimism, identity, meaning in life, and empowerment [19]. The approach goes beyond clinical concerns and includes supporting patients to live a fulfilled life. Physical health care that meets patients’ identified needs and goals is therefore an essential part of recovery-oriented care.

The Chronic Care Model describes how the community, health system, delivery system design, decision support, clinical information systems and self-management support combine in the chronic condition management and prevention structure [20]. As self-management is a key, but under-employed requirement of the Chronic Care Model, the Flinders Program [21] specifies a further 12 principles for implementing self-management support in primary care.

The Flinders Program comprises an overarching clinical, person-centred process underpinned by cognitive and behavioural theory and motivational techniques. It integrates self-management support and tailored evidence-based preventive interventions, as identified above, and is consistent with the Chronic Care Model principles of self-management support [22] and recovery-oriented care [23]. Existing research shows sustained behaviour change, in a range of populations, conveys better disease management, improved quality of life [22, 24–28] and preventive health benefits [29, 30].

### Piloting

Service use and pilot studies conducted by the current research team have showed feasibility, high acceptability and good retention in mental health services, and successful use of the Flinders Program in preventive health, justifying progression to a randomised trial for CVD risk reduction in SMI.

There are few existing trials of interventions that reduce absolute cardiovascular risk, rather than individual factors. Further, no effective interventions have been identified for integration into the Australian health care system. For the first time internationally, the Flinders Program will be used to integrate physical and mental health care by engaging patients in their own care through this chronic condition self-management care planning approach. The current trial protocol is presented in accordance with Standard Protocol Items: Recommendations for Interventional Trials (SPIRIT) (see Additional file 1 and Fig. 2).

## Methods/Design

Using the UK MRC guide on Developing and Evaluating Complex Interventions, we piloted the Flinders Program in patients with SMI with the aim of reducing CVD risk and improving quality of life. We now aim to test the intervention in a phase III randomised effectiveness trial (*N* = 358).

**Aim 1**
*Objective:* To evaluate the effectiveness and cost benefits of the Flinders Program to reduce absolute CVD risk and improve quality of life in SMI, using a randomised controlled trial design.

**Aim 1**
*Hypotheses:* The delivery of the Flinders Program for SMI will be associated with (1) reduced absolute CVD risk, (2) improved quality of life, and (3) will be cost effective.

**Aim 2:** To explore the requirements for a nationally sustainable translation of recommended physical health management in SMI, using qualitative methods which involves all key stakeholders, to develop a policy framework and a comprehensive implementation training package.

### Study design addressing aim 1

A 12-month 2-group randomised (see Fig. 2) controlled trial, with extended follow-up to 24 months will be conducted to contrast the Flinders Program intervention in addition to usual care, with usual care alone.

Each of the two groups will have approximately 178 participants. The intervention group will receive the Flinders Program, in addition to their usual care. Usual care will be provided by health professional care coordinators in public community mental health clinics. Intervention patients and trial nurses will use Flinders Program care planning tools to identify all CVD risk factors, chronic condition and psychosocial issues, patient-identified priority problems and goals, and consensus about which concerns require action.

### The Flinders Program intervention

The Flinders Program provides both framework and tools to engage the patient and structure self-management assessment, tailored planning, motivational enhancement, disease management, prevention, coordination and outcome measurement. It drives optimal use of current health services. In this trial, intervention-allocated participants will be supported to access existing structures and motivational processes including smoking cessation programs; clinical control of triglycerides and diabetes; one-on-one and group components of weight reduction programs; and, where applicable, initiation and adherence with BP-lowering and lipid medications.

Once training has been undertaken, any clinician can deliver the program; however, in the trial’s instance, mental health nurses will facilitate the intervention. Further, while the Flinders Program can be delivered face-to-face, it can also be provided by phone and/or electronically, according to patients’ needs. A web version of the program allows patients and trial nurses to develop the care plan either face-to-face or via the web. This permits communication in real time, or asynchronously via text or email, enabling monitoring and motivational enhancement. In circumstances where participants are randomised into the intervention and subsequently voice issues with continuing to participate in this group, accommodations are made for withdrawal from the intervention program. However, these participants are given the option to continue providing information at the scheduled follow-up data collection points. Details of intervention steps are provided in Table 1.

**Table 1 Tab1:** Summary of intervention schedule and components

Flinders Program component^a^	Planning and action for:	
	Condition management	CVD risk management
Assessment 1 (week 1) Flinders tools: Partners in Health (PIH), Cue & Response	Patient and trial nurse use Flinders tools to identify all risk factors, chronic condition and psychosocial issues and decide which require action.	Using additional tools and resources: • NVDPA *Guidelines for the Management of Absolute Cardiovascular Disease Risk* • Flinders Program health behaviour assessment tools • Trial nurse database of resources, • Nurse and patient review CVD risk and lifestyle and agree plan for behaviour change among: − Smoking cessation – details below − Diet and exercise – details below − Alcohol use – SA Alcohol and Drug Information Service (ADIS) resources − Lipid-lowering / BP medication via GP
Assessment 2 (week 2) Flinders tools: Problems & Goals (P&G), Flinders Care Plan		
Flinders Care Plan for following 6–12 months shared by trial nurse, patient, psychiatrist, mental health care coordinator and general practitioner (GP).		
Follow-up (week 1–4)	At flexible negotiated follow-up and review contacts (6 in total), the trial nurse: • Monitors outcomes of the care plan using PIH and P&G scores • Assists the patient to achieve goals using motivational and problem-solving approaches and informational and community-based resources • Uses the structured framework of the Flinders Program to coordinate care e.g.,: − as needed, assists access to identified disease specific services e.g. self- management education, home medication review, GP Management Plan and Team Care Arrangements, Chronic Disease Dental Scheme, as per care plan − as needed, assists access to services and coordinates communication between patient and services, social work, Occupational Therapist assessment, Patient Assistance Transport Scheme, financial counselling, local activity groups/courses, Disability Employment Services, Housing, other as per care plan • Reviews and updates Flinders Care Plan as required.	
Follow-up (week 6)		
Follow-up (week 8)		
Follow-up (week 12)		
Follow-up (week 16)		
Follow-up (week 20)		

^a^Assessments face-to-face and follow-ups face-to-face/phone/email/SMS to suit patient needs

### Study design to address aim 2

Concurrent with the trial, views of trial and health service staff, intervention patients, and their family carers will be explored via sequential interviews and focus group discussion (FGD). This will identify enablers and barriers within health systems, practitioner behaviours and patient perceptions, affecting implementation of recommended physical health management in people with SMI.

Twenty patients, 15 family carers and 12 health professionals will be interviewed at different stages of the trial (beginning, middle and end) to gather perceptions of the intervention as a process and outcome. Two FGDs will be also conducted with the health professionals to understand their overall experience at the conclusion of the trial.

### Study setting and study population

The sample population will be patients receiving, or who recently received, treatment and care from southern and western Adelaide community mental health clinics (population of approximately 360,000 patients), including clozapine clinics. Usual care in South Australia, and nationally, comprises monitoring responsibility by dedicated care coordinators trained as mental health professionals (psychiatrists, medical officers, psychiatric nurses, social workers, occupational therapists, and psychologists), referral to general practitioner (GP), if known, and recommendations to access community clinics and programs (all unevenly enacted). We will sample 358 participants in total (across both groups) to allow for an attrition rate of 15%.

### Inclusion and exclusion criteria

Participants will have a diagnosis of schizophrenia, schizoaffective disorder, bipolar disorder, or depressive psychosis established by extant clinical assessment and ICD-10 diagnostic codes; age at least 30 years which allows estimation of absolute CVD risk and matches patient age profile; and at least one CVD risk factor (overweight/obesity, smoking, high blood pressure, blood lipids, glucose or diabetes). However, those without ability to give informed consent; with low English literacy; and/or have acute psychosis or suicidality at baseline will be excluded from participating.

### Recruitment process

Patients will be alerted to the study by their mental health care co-ordinator or a letter from the study team who then will seek (eligible) patients’ permission for a trial nurse to contact them. If permission is granted by the patient, trial nurses will then make contact to provide further details about the RCT and extend an offer to them to participate in the study. Recruitment feasibility is high with 1-month prevalence of psychosis 0.4% in Australia. For example, 250 patients are closely managed for schizophrenia responsive to clozapine in the southern local health network region, with local data showing over 95% meeting risk factor criteria, and two community mental health clinics in this area which currently have 332 (Clinic 1) and 484 (Clinic 2) patients, many with psychoses and CVD risk factors. The western Adelaide health service region also includes large public mental health clinics beyond the southern area from where participants will be recruited if needed.

### Trial procedures

Figure 1 provides a preliminary CONSORT diagram of the study and participant flow. Baseline and follow-up psychometric and biometric data from all patients will be obtained by trial nurses at two main community mental health clinics. However, it is expected that a small number of participants may not be physically able to travel to health clinics; if this should eventuate, trial nurses will make alternative arrangements to facilitate collection of participants’ data. Blood will be taken by trial nurses (trained in phlebotomy) and processed by a community health pathology provider or a Point of Care analysis machine (Roche *cobas® b 101*) able to provide on-the-spot blood results for total and HDL cholesterol, and a glucometer will provide blood glucose levels. Body mass index-based risk scoring will be used if bloods are unattainable. Digital scales and a stadiometer were to used in order to calculate BMI, while a Bedfont *piCO™ Smokerlyzer* will be used to determine the proportion of carboxyhemoglobin (%COHb) and blood carbon monoxide concentration in parts per million (COppm). All data from biometric and psycho-social measures will be entered into the survey application, *Qualtrics,* on a tablet. Full survey data will also backed-up by downloading weekly into a password secured, university file folder.

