**Fig. 1 Fig1:**
[figure not shown]
Participant flow across two arms of the RCT

Post baseline, key patients’ details (Study ID, age, gender) will be sent to an independent clinical trials allocations unit who will be provided with computer-generated protocol for block randomising (i.e., stratified by age and gender) participants. Those randomised into the intervention arm will have their intervention delivered by trial nurses trained in the Flinders Program and study-specific interventions, as illustrated in Table 1. Once the initial Flinders Program assessments have been delivered (Cue & Response; Problems and Goals; see Additional file 2: Table S1), trial nurses will negotiate with participants whether contact is undertaken face-to-face or remotely (e.g., phone; email) on a case by case basis.

Expert Flinders Program trainers will monitor trial nurses by sampling care plans and will provide group and individual supervision initially weekly then monthly to maintain fidelity. Trial nurses will not provide services to ‘control’ group patients. For both groups, other services will continue as usual. However, if at any stage during the intervention, a given participant’s mental health declines to a level that warrants inpatient admission, or where they indicate that they do not wish to continue, s/he will be withdrawn from the trial without adverse impact on their usual care or relationship with the mental health services. The participant can elect to rejoin the trial once the problem is addressed. Post trial, data will be de-identified, and securely stored in a password protected university data repository. Subsequent requests for access to trial data will be considered and then approved/not approved by study CIs.

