### Randomisation and blinding

Consenting patients will be randomly assigned to intervention or control with 1:1 allocation ratio. Blocked randomisation within strata (median age, gender) will balance potential confounders and keep group sizes equal, and will use a standard permutated block algorithm to protect concealment. A statistician will independently generate random sequences for each stratum and provide this to a clinical trials allocations unit, independent from the research group, who will randomly allocate participants to intervention or control arm post baseline data collection. Patients cannot be blinded to receipt of the intervention but study information will present the equipoise position. The statistician and health economist will be blinded for comparison of the data sets. Once the final results have been obtained, unblinding is permissible to be able to report and disseminate the trial outcomes.

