### Outcomes measures

As shown in Fig. 2, outcome assessment at baseline, 6,12, 18 and 24 months: bloods and self-report outcomes will be collected by trial staff. Biometric measures constitute total and high cholesterol lipids, blood pressure, weight in kilogrammes, blood glucose level, height and waist measurement in centimetres, %COHb, blood COppm, which constitute the necessary information to calculate the General CVD Risk Score [31]. The self-report measures comprise quality of life [32] SF-12; psychological distress [33] K-10; the Alcohol Use Disorders Identification Test - consumption [34] AUDIT C-3; the Fagerström Test for Nicotine Dependence [35]; the Medical Outcomes Study Sleep measure [36] MOS Sleep; International Physical Activity Questionnaire [37] IPAQ; Australian dietary guidelines healthy eating quiz [38], Partners in Health [39, 40] PIH; Patient Assessment of Chronic Illness Care [41] PACIC; Singh O’Brien Level of Engagement Scale [42] SOLES. Hospital admissions will be extracted from service records to minimise burden on patients and health care staff.

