**Fig. 2 Fig2:**
[figure not shown]
Standard Protocol Items: Recommendations for Interventional Trials (SPIRIT) Figure of enrolment, treatment and assessments over time

Key outcomes will involve assessing change at 6, 12, 18 and 24 months for the following measures:Absolute CVD risk will be measured using the General CVD Risk Score [31]. This measure applies from age 30 years and includes gender, age, systolic blood pressure, smoking in last week (Y/N), diabetes (Y/N), hypertensive medication (Y/N), and either total and HDL cholesterol or body mass index (Aim 1, Hypothesis 1).Health-related quality of life will be measured by the SF-12 [32], a validated and commonly used instrument, producing summary scores for mental health and physical health components. The Australian SF-6D scoring algorithm developed by [name] and colleagues will be applied to generate utilities and calculate quality adjusted life years [43], (Aim 1, Hypotheses 2 and 3).

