
### Data and trial monitoring

The study team responsible for the day to day running of the RCT comprise a trial manager, two clinical trial nurses, an administrate support worker, and a PhD student.

A study management committee, chaired by the project lead, with participation from study team members and consumer representatives will meet approximately 3-monthly to oversee the study and ensure effective data management. The committee will also report any adverse event to the South Australian Clinical Human Research Ethics Committee following standard procedures. They will also monitor interim analyses conducted by the statistician and will make the final decision regarding the appropriate stage to terminate the trial.

A national advisory panel of mental health and cardiovascular health experts, and national consumer advocates will meet 6-monthly to provide high level advice to the research group. A stakeholder working group of service managers, psychiatrists, GPs, care coordinators, other clinicians, and consumer advocates with lived experience of mental illness and physical health problems will confirm pathways and agree clinical protocols for mental health, primary care and community providers to ensure sustainability, execution and ongoing communication during the trial. Patients and carers will also be consulted through the Southern Adelaide Mental Health Consumer and Carer Advisory Group.

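### Two unmasked trial nurses both deliver the programme and collect follow-up data, exposing parts of both primary outcomes to bias, and the role of carbon monoxide in the CVD score is not reconciled

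*Protocol article*

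**What the plan says.** **Who collects the data.** Trial procedures states: "Baseline and follow-up psychometric and biometric data from all patients will be obtained by trial nurses at two main community mental health clinics". This covers both arms and every follow-up visit.

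**Who delivers the programme.** The same section states: "Those randomised into the intervention arm will have their intervention delivered by trial nurses trained in the Flinders Program and study-specific interventions". It adds: "Trial nurses will not provide services to ‘control’ group patients".

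**How many nurses.** Under Data and trial monitoring, the day-to-day team is said to "comprise a trial manager, two clinical trial nurses, an administrate support worker, and a PhD student". No outcome assessor is listed.

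**Who is masked.** Randomisation and blinding says patients cannot be blinded, and then: "The statistician and health economist will be blinded for comparison of the data sets". No one who collects data is named as masked. Allocation follows baseline data collection.

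**How smoking enters the score.** Outcomes measures lists the biometric measures, ending with "COHb, blood COppm, which constitute the necessary information to calculate the General CVD Risk Score". A little further on, the definition of the General CVD Risk Score gives its inputs as gender, age, systolic blood pressure, "smoking in last week (Y/N"), diabetes, hypertensive medication, and either cholesterol values or body mass index. CO is not among them, and no rule connects the CO reading to the smoking item.

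**The concern.** A nurse who has worked with a participant on a care plan knows that participant's arm, and trial nurses provide no services to controls. When such a nurse later measures blood pressure, records smoking status or is present while the SF-12 is completed, two mechanisms can act. Knowledge of the arm can influence how a measurement is taken or recorded (detection bias). A participant who agreed a smoking-cessation goal with trial staff may be less willing to tell trial staff that they still smoke (response bias). Controls made no such agreement.

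The main outcomes are CVD risk and quality of life, and the plan allots a 2.5% Type I error rate to each primary outcome. Systolic pressure and smoking feed the first; the second is the self-reported SF-12. Masking the statistician cannot repair data that were biased when collected. Adjusting for the baseline value does not help either, because baseline precedes allocation and the exposure arises only at follow-up.

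The CO reading is an objective check on smoking that the trial already takes at its visits. As written, the article does not settle whether that check affects the score.

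**Working it through.** **1. The plan's own target.** Inputs from Statistical analysis: mean 10.5, SD 6, correlation 0.5, relative change 20%, 80% power, Type I error 2.5% per primary outcome.

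- Target difference: 0.20 × 10.5 = 2.1 points.
- Change-score SD: 6 × √(2 × (1 − 0.5)) = 6.
- n per group = 2 × 6² × ((2.241 + 0.842) / 2.1)² ≈ 155.2, so 156 per group and 312 in total. The stated 304 is within 3% of this; power at 152 per group is 79.1%.
- Attrition: 304 / 0.85 = 357.6, so 358, as stated.

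The sample size is not in dispute. The 2.1 points serve as the yardstick below.

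**2. What is exposed at follow-up.**

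| Item | Source in the article | Exposed? |
|---|---|---|
| Systolic blood pressure | obtained by trial nurses | yes |
| Smoking in last week | yes/no, source not stated | yes, unless CO decides it |
| SF-12 | self-report, collected by trial staff | yes |
| Lipids, glucose, CO | laboratory or device reading | not materially |
| Hospital admissions | service records | not materially |
| All baseline values | before allocation | no |

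**3. Size for the smoking item (illustration only).**

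From the article: mean score 10.5; 67% smokers, from the survey of Australians with psychotic disorders cited in Background. Assumed, with no source in the article: a smoker's score is k = 1.5 to 2.0 times a non-smoker's, and a fraction f = 5% to 20% more smokers in the intervention arm than in the control arm are wrongly recorded as non-smokers.

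- Non-smoker mean = 10.5 / (0.67k + 0.33). For k = 1.5 this is 10.5 / 1.335 = 7.87; for k = 2.0 it is 10.5 / 1.67 = 6.29.
- Smoker minus non-smoker gap = (k − 1) × non-smoker mean: 3.93 and 6.29.
- Spurious difference = 0.67 × f × gap.

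| f | k = 1.5 | k = 2.0 |
|---|---|---|
| 5% | 0.13 points (6% of 2.1) | 0.21 points (10%) |
| 10% | 0.26 points (13%) | 0.42 points (20%) |
| 20% | 0.53 points (25%) | 0.84 points (40%) |

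**4. Effect on false-positive risk.** With 152 per group and a two-sided 2.5% level, a false finding of benefit should occur 1.25% of the time. With SD 6, the standard error is 6 × √(2/152) = 0.688. A spurious 0.13 points raises the risk to about 2.0%, and 0.84 points raises it to about 15.5%. With the baseline-adjusted SD, 6 × √(1 − 0.5²) = 5.2, the range is 2.2% to 20.4%.

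No corresponding figure can be derived for blood pressure or SF-12 from the article.

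**The case against.** Several stronger readings are tempting, and the article does not support them.

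- *The nurses collect every outcome.* Hospital admissions come from service records, and blood values are laboratory or analyser readings that an assessor's opinion does not set.
- *Smoking enters by self-report and CO is ignored.* The item is worded like a question to the participant, but its source is not stated, and CO is listed among the measures said to supply the score. What stands is that the two statements do not fit together. A detailed coding rule could well sit in a fuller document; the mismatch between two statements in the article is still there to correct.
- *Each nurse questions her own caseload.* No such assignment is written, and one nurse might assess the other's participants. Equally, nothing provides for that separation. The article also does not say who enters answers on the tablet, so self-completion may already be the practice.
- *The bias certainly runs one way on both outcomes.* That is plausible but not shown. Controls may also deny smoking, which is why the calculation uses an excess rate.

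Timing also weakens the mechanism. The last scheduled contact in Table 1 is week 20, about seven months before the 12-month visit. This lessens the concern at later visits but does not remove it: the 6-month visit follows week 20 by about six weeks, and the care plan is meant to cover the following 6 to 12 months.

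Finally, the 67% comes from a survey of psychotic disorders, whereas the trial also admits bipolar disorder and sets a minimum age of 30. The prevalence in the trial may differ.

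**Conclusion.** The point holds in a limited form. As written, the trial nurses who deliver the programme also obtain follow-up data in both arms; there are two of them, and no masked or separate assessor is provided for. That exposes follow-up blood pressure, smoking status and SF-12, and so components of both primary outcomes, to detection and response bias. In addition, the two statements in Outcomes measures about what the CVD score needs must be reconciled on CO.

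For smoking alone, the illustration gives a spurious difference of 0.13 to 0.84 points, or 6% to 40% of the 2.1-point target. It rests on the assumed score ratio and excess false-denial rates, on the survey prevalence, and on CO not deciding the smoking item. A reader might infer that misrecorded smoking could account for a positive trial. Within this range it could not by itself produce the full 20% effect, though it could distort the estimate and raise the chance of a false positive.

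**What to change.** - **Smoking item.** State in Outcomes measures how CO and the yes/no item combine. In both arms and at every visit, score a participant as a non-smoker only if the answer is no and the CO reading is below a prespecified cut-off. This uses data already collected. CO reflects only recent smoking, so it is a partial check on a last-week item.
- **Assessment visits.** Roster follow-up so that no nurse assesses a participant she coached, and say so under Randomisation and blinding. The two existing nurses can cover this without extra staff. The price is less flexible scheduling. Masking will be imperfect because participants may disclose their arm.
- **Questionnaires.** State that participants complete the SF-12 and the other self-report measures themselves on the tablet. This removes the interviewer's influence but not response bias from participants who know their arm, which should be acknowledged as a limitation.
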